## Abstract

Closed reduction is a common treatment method for developmental dysplasia of the hip (DDH) in children aged 6–18 months. Residual acetabular dysplasia (RAD) is the most common complication associated with closed reduction. Residual limbus inversion (RLI) is a common condition following DDH closed reduction. Previously, we confirmed that when limbus inversion exceeds 32.2% of the acetabular depth after closed reduction, RLI persists and leads to RAD; however, this was based on a small cohort with a short-term follow-up period. The long-term fate of RLI and the correlation between RLI and RAD have yet to be verified. Therefore, this multicenter clinical study protocol was designed in three parts to investigate the effect of RLI on acetabular development after closed reduction of DDH (a multicenter retrospective cohort study), effect of RLI clearance on acetabular development (a multicenter retrospective and prospective randomized controlled study), and influence of inverted limbus clearance on acetabular development during DDH reduction (a multicenter prospective cohort study). Statistical analysis was performed by assessing the basic measures of acetabular development including the acetabular index and central-edge angle using frontal pelvic radiographs; the magnitude of limbus inversion, cartilaginous acetabular index, and T1ρ mapping values were measured using magnetic resonance imaging. The multicenter retrospective cohort studies required 5 years of follow-up period at minimum, and the prospective randomized controlled studies required reviews of frontal pelvic radiographs every 6 months as well as data pooling every 2 years to compare the short- and mid-term outcomes of hip joint morphological development between the two groups of pediatric patients. This research program is expected to verify that RLI following closed reduction of DDH can affect acetabular development and that limbus excision during DDH reduction can improve postoperative RAD. Therefore, the indication and timing of surgical intervention for RLI after closed reduction of DDH provide a basis for revising the acceptable criteria for utilizing closed reduction of DDH to reduce the incidence of osteoarthritis caused by RAD following DDH treatment.

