##### Prospective follow-up observation

2.2.2.3.

Prospective follow-up observation was performed for the two clinical cohorts, and frontal pelvic radiographs were reviewed every 6 months. Since development of the hip joint in children is a long-term process, the included pediatric patients needed to be followed until skeletal maturity. Data pooling was performed once every 2 years to compare the short-term and medium-term outcomes of hip joint morphological development between the two groups. MRI T1ρ mapping was used to quantitatively evaluate quality of the acetabular cartilage before and during postoperative follow-up. The evaluated aspects and parameters were the same as those specified in 2.2.1.

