##### Statistical analysis

2.2.2.6.

Fisher's precision probability test was used to compare the difference between the sexes and affected sides, using analysis of variance to compare the different ages between the surgical and non-surgical cohorts. Differences in acetabular index was compared using Student's *t*-test. Chi-square test was used to compare IHDI classification, VAS and HHS, and Severin classification at the final follow-up, and analysis of variance was used to compare the MRI T1ρ mapping values and the incidence of Grade III and Grade IV adverse events.

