##### Prospective follow-up observation

2.2.3.3.

The control and experimental cohorts were observed radiologically every 6 months during follow-up, and the short-, mid-, and long-term outcomes of hip joint morphological development were compared between the two groups of pediatric patients. Data pooling was performed once every 2 years, and clinical function tests, radiologic measurements, and MRI T1ρ mapping measurements were performed at the stage of skeletal maturity.

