At present, the changes and outcomes of the inverted limbus after closed reduction of DDH remain controversial. Severin et al. (23) believed that after achieving stable closed reduction, the inverted limbus would be gradually absorbed and disappear; however, others believed that the inverted limbus was a key factor leading to AVN. Previous studies have been based on indirect observation of x-ray images, and there is a lack of direct evidence regarding the morphological evolution of the inverted limbus. This study used serial MRIs to observe the outcomes of limbus inversion after closed reduction of DDH, which lessened the impact of radiation on pediatric patients and enhanced the safety and reliability of the study. Our previous findings indicated that the magnitude of limbus inversion after closed reduction is closely related to its medium-term morphological outcome (16). However, the previous study had certain limitations since it was based on a small sample and did not follow-up until skeletal maturity. Previous studies have confirmed that a primary limbus inversion leads to primary acetabular dysplasia and early-onset OA (24, 25), but the long-term result of RLI has not been reported in DDH patients who previously underwent closed reduction.

Reaching skeletal maturity of the hip is a long-term process; therefore, the prospective design of this protocol better reflects the relationship between RLI and multiple prognostic outcomes while balancing many known or unknown biases. This research plan is to be led by the corresponding author's institution and carried out by multiple clinical research centers in cooperation with pediatric orthopedic centers in China. Compared to previous case-control studies, this study was designed as a multicenter clinical study with a higher level of evidence. Consistency of the characteristics included in a multicenter sample study is a key issue in clinical research. In the process of sample collection, cohort characteristics within each center are required to achieve homogeneity, which can be solved by increasing the sample size to ensure reliability of the final pooled samples. The follow-up rates in clinical studies are another key issue affecting reliability of the study results. Specialized staff in each center were assigned the task of following included cases, establishing case study databases, and recording various contact methods to guarantee a follow-up rate of over 80%.

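### In the randomised part, the acetabular index can be read from films every 6 months, but the only analysis named is a t-test with no time point, which leaves intermediate films unused and is exposed to bias from arm-dependent loss

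*Protocol article*

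**What the plan says.** The point concerns the randomised comparison of clearance surgery with no surgery (section 2.2.2).

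- **Overview (Abstract).** "the prospective randomized controlled studies required reviews of frontal pelvic radiographs every 6 months as well as data pooling every 2 years". The Abstract names no test for the index.
- **Schedule (2.2.2.3).** "frontal pelvic radiographs were reviewed every 6 months", and "the included pediatric patients needed to be followed until skeletal maturity".
- **What is read (2.2.2.3).** "The evaluated aspects and parameters were the same as those specified in 2.2.1". Section 2.2.1.3 lists the acetabular index among those measurements.
- **Comparison (2.2.2.3).** "Data pooling was performed once every 2 years to compare the short-term and medium-term outcomes of hip joint morphological development".
- **Outcome (2.3.1).** Improvement of the index is the first of four primary outcomes. Section 2.2.1.4 also calls it the most suitable indicator.
- **Test (2.2.2.6).** "Differences in acetabular index was compared using Student's" t-test. No time point, baseline adjustment or repeated-measures model accompanies it. The phrase on final follow-up in the next sentence belongs to the chi-square tests.
- **Retention.** The Discussion speaks of "recording various contact methods to guarantee a follow-up rate of over 80" per cent. The part 1 sample size allows for 20% loss.

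**The concern.** The design produces a series of readings per child, and the named test takes a single number per child. Whichever number is chosen, something is given up.

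- **Value at a fixed time.** A child without a film at that time contributes nothing, although earlier films exist.
- **Change from entry to a fixed time.** The entry film is used, but the films between are not, and the same children are lost.
- **Last available film.** All children stay in, but they are compared after different lengths of follow-up on an index that changes with growth.

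This matters more here than in a blinded trial. The comparison is open, guardians may withdraw at any time (4.1), and 2.2.2.1.1 says that an index above 30° usually leads to pelvic osteotomy. Families of non-surgery children with worsening films could plausibly leave follow-up. Loss would then depend on earlier films, and differently in the two arms. At stake are the size of the effect on a primary outcome and some precision.

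**Working it through.** **Inputs from the protocol article.** Section 2.2.1.4: index 21.41° (SD 3.61) and 18.88° (SD 4.32), alpha 0.05, power 0.9, 1:1 allocation, 20% loss. Section 2.2.2.3: films every 6 months. No separate sample size is given for the randomised part, so the part 1 figures are borrowed as a scale.

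**1. The plan's own figure.** Difference = 21.41 − 18.88 = 2.53°. SD = √((3.61² + 4.32²)/2) = 3.98°. With two-sided alpha (sidedness is not stated), n = 2 × (1.960 + 1.282)² × 3.98²/2.53² ≈ 52.0, rounded up to 53 per group. Then 53/0.8 = 66.25, so 67. The stated 67 is reproduced, and the sample size is not in question.

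**2. Precision when loss is unrelated to the index.** Assumptions: 53 per arm before loss, entry plus 8 six-monthly films, SD 4.3° at 4 years, adjacent-visit correlation 0.77, about 20% lost. Completers per arm = 53 × 0.8 = 42.4, so the t-test standard error is about 4.3 × √(2/42.4) = 0.93°. Simulation gave 0.94° for the t-test and 0.89° for the mixed model. Variance saved = 1 − (0.89/0.94)² ≈ 10%. In the plan's calculation, 53 is the number after loss; using it before loss raises both standard errors but should hardly change their ratio.

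**3. Bias in a completers' t-test on the final value.** Assumptions: entry plus 4 six-monthly readings, SD 3.98°, constant within-child correlation 0.5 to 0.8, an effect that builds evenly to 2.53°, 20% loss by 24 months, and 200,000 simulated children per arm. Where loss depends on the last reading, the log-odds of leaving change by 1 per SD.

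| Loss mechanism | Completers' difference | Using all readings |
|---|---|---|
| Random | 2.52–2.53° | 2.52° |
| Depends on last reading, same in both arms | 2.52–2.54° | 2.52–2.55° |
| Depends on last reading, control arm only | 1.91–2.10° | 2.50–2.52° |
| Depends on last reading, opposite directions | 1.30–1.76° | 2.53–2.55° |

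The shortfall runs from none to 2.53 − 1.30 = 1.23°. In the setting of step 2, let non-surgery children more than 2° above the mean at the last film leave at 9% per visit and the others at 1.2%. The completers' difference is then 1.93°, or 1 − 1.93/2.53 = 24% too small, and the mixed model gives 2.53°.

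**4. If improvement is what is tested.** In a further simulation with arm-dependent loss of about 20% over four visits, the t-test on the final value gave 2.00°, but the t-test on change from entry gave about 2.51°. Under longer follow-up and heavier loss, the change analysis also fell, to about 1.99°. The model on all readings stayed at about 2.53° throughout.

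**5. If the last available film is tested.** Suppose the effect builds evenly over four visits and 5% of the starting children leave at random in each interval. Those who leave carry 0, 1/4, 1/2 and 3/4 of the effect. The expected difference is 2.53 × (0.80 + 0.05 × (0 + 0.25 + 0.50 + 0.75)) = 2.53 × 0.875 = 2.21°. This is a mixture over follow-up lengths, not the effect at any one time.

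**The case against.** The strongest reply is that the article does not say what a critic might infer from it.

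- **Three of every four films unused.** A reader might infer this from 6-monthly films and 2-yearly poolings. The t-test is not tied to the poolings, and pooling may simply mean merging the centres' data to date, with every film included. The inference is not supported as a fact of the plan.
- **Children lost early are excluded.** This too is not stated. It follows only if the test is run at a fixed time.
- **The same fault in part 3.** Section 2.2.3.3 says "The control and experimental cohorts were observed radiologically every 6 months during follow-up", but places the radiologic measurements at skeletal maturity. A 6-monthly index series is not established there.
- **The outcome is improvement.** A t-test on change uses the entry film and, with loss near 20% over four visits, showed almost no bias. This stands and limits the size of the point.
- **The bias depends on assumed loss.** It disappears if loss is random or acts alike in both arms. The 20% belongs to part 1, and the 80% is a retention target backed by dedicated staff. A mixed model recovers the truth in these simulations because they satisfy its missing-at-random assumption.
- **Details may sit in the data analysis plan mentioned in 4.2.** That is fair for missing-data rules, whose absence is no finding here. It does not cover the t-test, which is a method the article states.

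**Conclusion.** The point holds for the randomised part. A two-sample t-test without a time point is a poor match for a primary outcome that can be read every 6 months. It cannot use the series jointly, and each way of choosing the single number has a cost.

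The certain loss is modest: about 10% of variance under the assumptions of step 2. The possible bias is larger but conditional. A final-value analysis of completers fell short by about 0.4° to 1.2° on 2.53° when about 20% loss depended on earlier films differently by arm. There is no bias at a fixed time with random loss, and much less when change from entry is analysed, unless follow-up is long and loss heavy. Follow-up to skeletal maturity makes long follow-up the intended setting. The correlations, loss mechanisms and use of part 1 figures are assumptions. The change is worth making because it corrects a stated method at little cost, not because bias has been shown.

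**What to change.** In 2.2.2.6, replace the t-test on the acetabular index as follows.

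1. Name one time since randomisation for the primary comparison.
2. Estimate the arm difference at that time with a likelihood-based mixed model for repeated measures. Use the entry and all 6-monthly readings up to that time from all randomised children, with entry index, arm, visit, arm-by-visit interaction and a within-child covariance.
3. State that the estimate is valid under missing at random.

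Leave 2.2.3.4 unchanged unless the index is in fact measured every 6 months in part 3. If it is, the same kind of model can serve there.

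**Cost.** The change is to the analysis wording. SPSS 27, the software named in 2.2.1.4, fits such models, and no new films are needed. A covariance structure must be chosen. An unstructured one has v(v + 1)/2 parameters: 10 for 4 follow-up visits, 36 for 8 and 210 for 20. With many visits, a parsimonious structure should be named in advance.

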**Clinical Trial:**
http://www.chictr.org.cn/showproj.aspx?proj=35045 (ChiCTR1900020996)

## Introduction

1.

Closed reduction is a common method for treating developmental dysplasia of the hip (DDH) in children aged 6–8 months; however, re-dislocation after reduction, avascular necrosis, residual acetabular dysplasia (RAD), and other complications cannot be completely avoided (1). Among these, RAD is the most common complication of DDH closed reduction treatment. A prospective multicenter study conducted by Sankar et al. (2) found that even with stable closed reduction, approximately 11% of children still had residual dysplasia, and long-term follow-up results of a study by Terjesen (3) noted a higher statistic of up to 38%. RAD is the main cause of osteoarthritis (OA) in young adults (4, 5) which often requires total hip replacement (THR). Approximately 9.1% of THR is caused by RAD, and among young adults, this proportion is as high as 21%–29% (6, 7). Therefore, prevention of RAD after DDH treatment and timely correction of RAD are key to long-term prevention of OA.

The causes of RAD in children after closed reduction for DDH are complex. Age, dislocation height, and acetabular index at reduction are commonly used clinical indicators to predict RAD (3, 8, 9), but these factors can only partially explain the causes of RAD from clinical phenomena. Several factors affect the development of the acetabulum after closed reduction. In addition to the genetic quality of DDH, the quality and development potential of the acetabular cartilage, the soft tissue in the acetabulum, and the evolution of the concentric relationship between the acetabulum and femoral head are related to the shaping ability of the hip joint. A relevant understanding of the internal causes of RAD and timely intervention are of clinical significance for the prevention of OA caused by RAD. Previous clinical studies based on indirect radiological observations cannot directly reflect real world practice, in which the non-bone structure and concentric evolution of the hip joint must be considered. Radiological observations can be used to monitor acetabular development; however, they cannot accurately predict RAD (10, 11). Therefore, a method for follow-up observation of hip joint development is warranted to enable better clinical understanding of RAD.

It is generally accepted that the labrum is a tough fibrocartilaginous structure attached to the rim of the osseous acetabulum. Before skeletal maturity, it is characterized by non-ossifying soft tissue which helps to stabilize the femoral head into the acetabulum until osseous acetabular rim merge (12). Limbus inversion remains a common phenomenon after closed reduction, which increases the gap between acetabular and femoral head combined with ligamentum teres, and reduces the quality of closed reduction regarding to concentricity. That's why clearance of interposition (inverted limbus and ligamentum teres) is beneficial to sustain the concentricity and acetabular development. But the everted part of limbus was reserved to keep the potentiality to osseous acetabular rim. It's our negligence that ambiguous expression makes you confused about the management. we have made correction into our manuscript as follow. Clearance of interposition is performed by a standard anterior and superior approach to the hip, and remove ligamentum teres, the transverse ligament of the acetabulum and inverted limbus without the everted portion.

Magnetic resonance imaging (MRI) can display all bone and non-bone structures of the hip joint from multiple planes; therefore, it is useful for observing development of the acetabulum after closed reduction of DDH. However, MRI is commonly used to evaluate the pathological morphology of DDH before reduction and is seldom used for long-term follow-up (13, 14). In 2020, we published prospective MRI long-term follow-up results after closed reduction of DDH and established that “safety” (a reduction which could be maintained by the abduction of <65°) and “stability” (Ramsey safe zone >30°) are acceptable closed reduction standards (15). Owing to shaping of the pathological structure of soft tissue after reduction, non-concentric reduction of the DDH can gradually achieve concentric reduction. Additionally, we found an interesting phenomenon during follow-up using serial MRI: the inverted limbus was not absorbed overtime; instead, it was compressed into a thin layer of fibrous tissue inter-positioning in the superior joint space (15). Previous radiographic studies have shown that the inverted limbus can be absorbed and can disappear with gradual “docking” of the femoral head after reduction, but this is not the case. Intraoperative arthrography has shown that the inverted limbus is a hypertrophic filling defect with a widening superior joint space (Figure 1A); although this cannot be observed during the course of medium-term follow-ups (Figure 1B), MRI can reveal the residual inverted limbus as a thin layer of hypointense tissue embedded in the superior joint space (Figure 1C), as confirmed during surgery correcting for RAD (Figure 1D). This phenomenon has not been reported previously.

## Methods and analysis

2.

### Objectives

2.1.

Limbus inversion is a common pathological change in DDH; however, how does the RLI evolve after closed reduction, and how does it affect development of the acetabulum? To date, there have been no reports addressing these questions. Whether RLI affects the development of other aspects of the hip joint, whether surgical intervention is required, and whether acetabular dysplasia can be reversed after intervention are practical issues that must be addressed urgently. In light of the limitations of our previous study, we aim to address these issues through a retrospective and prospective multicenter randomized controlled study. The main purpose of this study is to clarify the long-term outcome of RLI after DDH closed reduction and its impact on development of the acetabulum. We aim to determine the appropriate indication and timing of surgical intervention for RLI after DDH closed reduction and to provide a basis for revising the acceptable criteria for closed reduction of DDH, to reduce the incidence of OA caused by RAD after DDH treatment.

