##### Selection of participants for the retrospective study

2.2.2.1.

To maximize the use of the peak ossification potential of acetabular cartilages in patients before the age of 5 years, pediatric patients who underwent successful closed reduction between 6 and 18 months that had experienced RLI and were ≤5 years old at follow-up were selected as study participants, given that it is more instrumental to observe the reversibility of delayed acetabular cartilage ossification. The frontal pelvic radiographs and MRI images of the hip joint were taken during follow-up to evaluate limbus inversion. The trail is illustrated in a flowchart as shown in Figure 5.

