###### Inclusion criteria

2.2.2.1.1.

Inclusion criteria 1–5 are the same as the previously listed inclusion criteria 1–5 (2.2.1.1);

6. More than 1 year after closed reduction;7. Patients aged ≤5 years at follow-up;8. The magnitude of limbus inversion exceeded 32% of the horizontal depth of acetabular roof at follow-up (or the cut-off value obtained in Protocol 2.2.1);9. The acetabular index was ≤30° at follow-up (since an acetabular index>30° usually necessitates pelvic osteotomy).

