##### Randomized blocks and interventions

2.2.2.2.

A randomized trial study design was the most appropriate approach to observe the efficacy of surgical intervention, with blinding techniques used during statistical analysis of the data. A double-blind study was not feasible because the surgeon was required to provide detailed information on the surgical regimen. The researchers in each center divided the RLI participants into two study cohorts based on the randomized block design, i.e., the surgery and non-surgery groups. After informed consent was obtained from the guardians of patients in the surgery group, clearance of the inverted limbus *via* arthrotomy was performed.

All surgeries were performed by pediatric hip joint surgeons with senior job titles *via* a bikini incision, and the inverted limbus tissue embedded between the acetabulum and femoral head was excised after arthrotomy without damaging the limbus-cartilage complex. After surgery, casts or braces were applied to immobilize single hips in abduction for 4 weeks and the patients gradually resumed walking after removal of external fixators. No special rehabilitation therapy was administered.

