The incidence of DDH in China is 1.52% (26).The large basis of the annual newborn population and the large number of patient samples in China are conducive to effectively accumulating study samples within a short period of time, which increases the feasibility of this study protocol. Our research question stems from novel ideas in clinical practice, and this study is the first to suggest that the inverted limbus cannot be absorbed after closed reduction for DDH and is a risk factor of RAD. This study is also the first to discuss the effects of RLI based on clinical practice. By conducting this study, we aim to clarify the effect of RLI on acetabular development after closed reduction of DDH, define the timing and indications for surgical interventions of RLI after closed reduction of DDH, and to inform revision of the criteria for an acceptable closed reduction in DDH treatment so that the incidence of OA caused by RAD after DDH treatment can be reduced in clinical practice.

The exact mechanism by which RLI causes RAD after closed reduction for DDH remains unclear. Wang et al. (27) used latex pads to simulate the inverted limbus embedded between the femoral head and acetabulum of the model hip joint and performed mechanical experiments to confirm that the local contact pressure at the location of the latex pads was significantly increased. Hence, we speculated that persistent imbalance in pressure between the acetabulum and femoral head caused by RLI after closed reduction for DDH is a major factor contributing to RAD. In future studies, we will further perform biomechanical experiments at the cellular level using animal models to provide insights into the mechanism of action of RAD in limbus inversion. It is of great clinical significance to reveal the molecular mechanism by which RLI causes acetabular dysplasia and to obtain robust evidence to guide clinical decisions.

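### The programme claims to determine the timing and indication of RLI surgery, but no part compares earlier with later clearance, and the surgical cut-off is applied rather than tested

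*Protocol article*

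**What the plan says.** Section 2.1 first names the long-term outcome of RLI and its effect on the acetabulum as the main purpose, then adds: "We aim to determine the appropriate indication and timing of surgical intervention for RLI after DDH closed reduction". The Discussion restates this as an aim to "define the timing and indications for surgical interventions of RLI after closed reduction of DDH", and the abstract links indication and timing to revised criteria for closed reduction.

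The three parts bear on this aim as follows.

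- **Part 1 (2.2.1, retrospective cohort).** Section 2.2.1.4 uses an ROC curve to find the initial inversion magnitude that predicts persistent RLI. Children who had repeat surgery are excluded.
- **Part 2 (2.2.2, randomised).** Eligibility includes "The magnitude of limbus inversion exceeded 32% of the horizontal depth of acetabular roof at follow-up" (or the Part 1 value), "More than 1 year after closed reduction", "Patients aged ≤5 years at follow-up" and an acetabular index of at most 30°. Allocation is "based on the randomized block design, i.e., the surgery and non-surgery groups". The reason given for the age limit is "To maximize the use of the peak ossification potential of acetabular cartilages in patients before the age of 5 years". Section 2.2.2.6 lists two-group comparisons, and age enters only as a between-arm check: "using analysis of variance to compare the different ages between the surgical and non-surgical cohorts".
- **Part 3 (2.2.3, prospective cohort).** Hips above the cut-off at reduction have open reduction with excision of the inverted limbus. Hips below it, or with no inversion, have closed reduction. The two cohorts are then compared.

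**The concern.** A claim about timing needs comparable hips cleared earlier and later. A claim about indication, in the sense of where the threshold should lie, needs the effect of surgery at different inversion magnitudes, ideally on both sides of the cut-off. The article describes neither contrast.

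This matters because a positive Part 2 result would be an average effect in children above one cut-off. Read against the stated aim, it could be taken as evidence for a particular time to operate and a particular threshold in young children, when neither had been compared with an alternative. The article's own rationale, ossification potential before age 5, makes it plausible that the effect depends on age at entry, so readers will want an answer on timing and may take the average result as one.

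**Working it through.** **1. Timing, part by part.**

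- Part 1 observes hips after closed reduction and excludes repeat surgery, so it has no surgical timing to compare.
- Part 2 randomises whether surgery is done, not when. There is no deferred arm. All clearance takes place more than 1 year after reduction and at age 5 or younger.
- Part 3 clears the limbus at the initial reduction, but the comparison group is hips below the cut-off, not hips cleared later.
- No comparison of Part 2 with Part 3 is described. It would not be like with like: Part 2 selects hips whose inversion is still above the cut-off more than 1 year on, whereas Part 3 selects on inversion at reduction, before it is known which hips would resolve.

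**2. Threshold, part by part.**

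- The Part 1 ROC outcome is persistence of RLI. A value that best separates persistent from resolved inversion need not be the value above which surgery helps.
- The ROC uses initial magnitude, measured on arthrography (2.2.1.3). Part 2 applies the value to magnitude at follow-up, measured on MRI (2.2.2.1.2).
- Part 2 randomises no hips below the cut-off.
- In Part 3 treatment is fixed by magnitude, so a difference between cohorts mixes the effect of treatment with that of initial severity.

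**3. The plan's own sample size.** The article gives one calculation, in 2.2.1.4 for Part 1. Inputs: means 21.41° and 18.88°, SDs 3.61° and 4.32°, α 0.05, power 0.9, ratio 1:1, loss 20%. Two-sided testing is assumed because sidedness is not stated.

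- Difference: 21.41 − 18.88 = 2.53°
- SD: √((3.61² + 4.32²)/2) = 3.981°
- n per group: 2 × (3.981 × (1.960 + 1.282)/2.53)² = 52.03, rounded up to 53
- With loss: 53/0.8 = 66.25, rounded up to 67

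The stated 67 per group (134 in total) reproduces. It is sized for one two-group difference.

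**4. What exploratory interaction terms could show.** No size is given for Part 2. Assume, for illustration only, 67 per arm (53 evaluable), the same SD, and two equal halves by age or by magnitude.

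- SE of the main effect: √(2 × 3.981²/53) = 0.773°
- SE of the difference in effect between halves: √(4 × 3.981²/26.5) = 1.547°, twice as large
- 95% interval half-width for that difference: 1.96 × 1.547 = 3.03°

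| Difference in surgery effect between halves | Power |
|---|---|
| 1.27° (half the main effect) | 13% |
| 2.53° (equal to the main effect) | 37% |
| 5.06° (twice the main effect) | 91% |

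Power for a 2.53° surgery effect within one half is 64%. For 90% power on a 2.53° interaction, the evaluable number per arm is 4 × 52.03 = 208.1, rounded up to 209. With 20% loss, 209/0.8 = 261.25, rounded up to 262 per arm, or 524 in total.

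**5. The enrolled age range is not settled.** Part 2 carries over Part 1's criterion of more than 5 years of follow-up. With reduction at 6 months at the earliest, that implies an age above 0.5 + 5 = 5.5 years, which conflicts with the limit of 5 years. The two criteria must be reconciled before the ages to which a result applies can be stated.

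**The case against.** The strongest reply is that indication and timing are aims of the whole programme, not of the randomised part alone. Part 1 finds a cut-off, Part 2 tests clearance above it, and Part 3 studies clearance at reduction. Enrolling only patients above a threshold is an ordinary enrichment choice. Much of this stands. A reader might infer that the programme can say nothing about indication, and the documents do not support that: Part 2 tests by randomisation whether clearance helps children within a defined set of limits on inversion, acetabular index, age and time since reduction. What remains untested is whether that cut-off is the right one.

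A second reply is that interaction and subgroup analyses belong in an analysis plan, and section 4.2 mentions one that is not shown. This also stands. Their absence from 2.2.2.6 is not the defect, and because the article does not name the blocking factor, it cannot be said that age is ignored in the allocation. But no analysis plan can create a deferred-surgery arm or randomise hips below the cut-off. The mismatch is between the stated aim and the stated design.

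A reader might also infer from the age-5 rationale that pooling across ages dilutes the effect by some definite fraction. The documents give neither the distribution of entry ages nor a relation between benefit and remaining growth, and the age criteria themselves conflict. No dilution figure can be supported.

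**Conclusion.** The point holds in limited form. On timing, no part compares earlier with later clearance in comparable hips, so the aim cannot be met by this design. On indication, Part 2 can test whether clearance helps hips above one pre-set cut-off at the ages enrolled, but the programme cannot validate the cut-off: it is derived for persistence, no hips below it are randomised, and Part 3 ties treatment to magnitude.

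These conclusions follow from the design as described and need no numerical assumption. The 37% power figure is only a guide to how little an interaction analysis could settle. It assumes that Part 2 enrols Part 1's 67 per group, that Part 1's SD applies, and that the modifier splits the sample evenly. Age at entry is not randomised, so even a precisely estimated age interaction would compare older with younger children and would not show that operating earlier on the same child is better.

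**What to change.** 1. In 2.1 and the Discussion, limit the claim to the effect of clearance in hips above the entry cut-off at the ages enrolled. State that earlier versus later surgery and the choice of cut-off are not tested. Bring the abstract's sentence on indication and timing into line.
2. In 2.2.2.6, pre-specify treatment-by-age-at-randomisation and treatment-by-baseline-inversion terms for the acetabular index. Keep both modifiers continuous, report estimated effects with intervals across the enrolled ranges, and label the analyses exploratory.
3. Reconcile the inherited follow-up criterion with the age limit, so that the ages to which the result applies are defined.

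The cost is reworded objectives and two model terms from data already collected. The downside is that the interaction estimates will be imprecise and must be reported as such. Sizing Part 2 for an interaction as large as the main effect would take about 262 per arm on the assumptions above, against 67 for the main effect, so narrowing the claim is the proportionate course.
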